#### The internal quality assurance process intervention for midwifery education

The intervention consists of an internal quality assurance process to be integrated in education institutions to enhance the quality of midwifery education. Through a recurrent self-assessment, the faculty assess their respective education programmes against national and international standards [22]. The faculty within the midwifery education programmes internally analyse the achievements of the self-assessment, indicating which standards are met, partially met, and unmet and what changes need to be prioritized in the next cycle. Based on the yearly self-assessment findings, the faculty make a recurrent activity plan. The learning from one assessment guides the plan that follows [23].

The implementation strategies include the following steps:

Update an existing tool to become a quality assurance assessment tool. The updated tool will be aligned with the new International Confederation of Midwives education standards [6] and the Bangladeshi accreditation standards for midwifery education programmes [9,11,17].

Train quality assurance task force committee members, consisting of midwifery educators (*n* = 21) selected by the government, representing both public and private education institutions. They will be trained on the quality assurance assessment tool during a four-day workshop. Upon completion, they will collect baseline data from all 31 sites.

Implement the Plan-Do-Study-Act (PDSA) cycle at all 31 institutions. The PDSA cycle is a four-step approach commonly used for quality improvement [23]. Through this approach, education institutions can ensure that their midwifery programmes meet education standards, fostering an environment of continuous improvement in midwifery education. The following steps will be applied:

Initially, the faculty members, such as educators, clinical supervisors, midwifery students, and library, computer lab, and clinical simulation managers, will conduct a yearly self-assessment of their education programmes against education standards. Following the self-assessment, an internal analysis of the findings will identify which areas require prioritization for improvement. This will provide a clear understanding of the changes needed to meet the standards.

In the Plan phase, based on the self-assessment, the faculty will develop an activity plan. This plan will address the prioritized areas for improvement, outlining specific actions and strategies to be implemented over the coming year to reach the standards.

In the Do phase, the faculty will execute the activity plan and conduct the next assessment about nine months later.

In the Study phase, the collected data will be analysed after the subsequent assessment has been conducted. The results will show whether the previously set standards were met, whether the recommended improvements were adopted, and whether any remaining needs were identified.

In the Act phase, based on the self-assessment findings, the activity plan will be reviewed. Insights gained from each cycle of the assessment will guide the subsequent cycle. In this process, the activities will be adopted, adapted, or abandoned. The continuous internal feedback loops will ensure that midwifery education is aligned with education standards [23].

Conduct an endline assessment at each institution using the quality assurance assessment tool and the self-assessment tool for midwifery educators and final-semester students. This evaluates the implementation process and the progress made in reaching the national accreditation standards in midwifery education (Figure 2).

**Figure 2. f0002:**
[figure not shown]
Overview of the implementation strategies.

### Data collection

Both quantitative components, using three self-assessment tools, and qualitative data, using focus group discussions (FGD), will be used [20].

#### Quantitative data

To measure the extent to which education standards are being met in the internal quality assurance process at the education institutions, a validated internal quality assurance assessment tool will be used [22]. The tool consists of 56 statements across six categories, built on International Confederation of Midwives Global Standards for midwifery education: i) Programme governance; ii) Faculty; iii) Students; iv) Midwifery programme and curriculum; v) Resources; and vi) Quality improvements [22], including scoring alternatives ‘Meeting the standard’, ‘Partially meeting the standard’, and ‘Unmet standard’. A team at each site, selected by the principal, will collaboratively complete the tool to ensure a comprehensive assessment of the current situation at each institution. The team may consist of educators, clinical supervisors, librarians, persons responsible for the computer lab and the clinical simulation lab, and midwifery students.

To determine the effectiveness of the internal quality assurance process in producing competent and confident midwifery educators, a digital self-assessment tool that has been contextualized and validated for Bangladesh in English and Bangla will be used. This tool records midwifery educators’ self-assessed confidence and competence in delivering the World Health Organization’s educator competencies [24,25]. The tool consists of 97 items distributed across nine core competencies and includes socio-demographic and work-related questions. The government will distribute the digital self-assessment tool to all midwife educators (*n* = 170–230) at the selected institutes following their consent to participate.

To evaluate the effectiveness of the internal quality assurance process in producing competent and confident midwives, a digital self-assessment tool in Bangla will be developed. The existing tool is based on the 2014 International Confederation of Midwives Essential Competencies [26] and is validated by the World Health Organization South-East Asia Region [25] for professional midwives, and the contextual items will be modified for use among midwifery students in Bangladesh. It will include 230 items across the seven core competencies, including a seven-point Likert scale for items, a socio-demographic profile section, and some contextual questions. This tool will be administered by the quality assurance task force committee to all final-semester midwifery students (*n* = 775–1550) following their consent. The latter two tools will be distributed at each selected institution at two time points: at the start of the study (baseline) and at the end of the study (endline).

#### Qualitative data

Focus group discussions (FGD) will be conducted to identify contextual factors that influence the internal quality assurance process and the mechanism of impact influencing the implementation of the intervention. Ten FGDs will be conducted comprising six to eight participants representing two education institutions that scored themselves at a higher level using the quality assurance self-assessment tool [22], three institutions that scored themselves at a medium level, and five that scored themselves at a lower level. In addition, FGDs (*n* = 4) will be conducted with the quality assurance task force committee members.

An interview guide will be developed guided by the principles of process evaluations of complex interventions [20], and one interview guide will be designed to cover the International Confederation of Midwives Global Standard for midwifery education [6]. All FGDs will be conducted in English and will be audio recorded.

### Data analysis

Quantitative data will be entered into IBM’s Statistical Package for Social Science (SPSS) Statistics (version 25) for descriptive statistics (frequencies, percentages, mean, and standard deviation). Overall scores of the quality assurance assessment tool will be categorized as low-standard (<60%), medium-standard (60% - <80%), or high-standard (≥80%). Low scores indicate significant resources needed, medium scores suggest moderate resources, and high scores imply fewer resources needed to meet Bangladesh’s national accreditation standards [9,17,22].

For the self-assessment tools for midwifery educators and students, the self-assessed confidence and competence scores will be calculated for each core competency. Principal component analysis will be used for data reduction, while frequencies, percentages, means, and standard deviations will be calculated to describe the socio-demographic and/or work profiles of the participants [27]. Non-parametric chi square tests will be performed to explore associations between the socio-demographic variables and the confidence and competence scores. Correlations between confidence and competence scores will also be explored. Based on the results, regression models will be used.

Qualitative data analysis will follow the principles of content analysis, based on Elo and Kyngäs [28]. The process involves reading through the entire text multiple times to understand it in its entirety, identifying meaning units answering the aim, and thereafter, coding and categorization.

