#### Setting

Midwifery education in Bangladesh is currently delivered at 147 institutes (60 public, 87 private) across the country, consisting of 60% clinical practice and 40% theory leading to a diploma degree after three years of study. Each of these programmes admits 25 to 50 students annually, attracting students from rural and urban areas. The educators hold a PhD or master’s degree, either in Sexual Reproductive and Perinatal Health, Hospital Management, Women’s Health, Nursing, or Public Health [11,14,21]. The internal quality assurance process will be initiated in 31 of the 147 public and private education institutions selected by the government of Bangladesh. The United Nations Population Fund in Bangladesh and the Swedish Development Cooperation Agency support these institutions in strengthening midwifery education and services in the districts where they are located.

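### The planned chi-square tests ignore that students and educators are nested in 31 institutions; false positives can inflate several-fold for institution-level variables among students, and far less elsewhere

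*Protocol article*

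**What the plan says.** The Setting section fixes the number of sites: "The internal quality assurance process will be initiated in 31 of the 147 public and private education institutions". On programme size it says: "Each of these programmes admits 25 to 50 students annually".

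Under Quantitative data, both surveys cover whole sites. For students: "This tool will be administered by the quality assurance task force committee to all final-semester midwifery students", with a stated total of 775–1550. The educator tool goes to all educators at the selected institutes, stated as 170–230. Both tools collect a socio-demographic profile. The educator tool adds work-related questions and the student tool adds some contextual ones.

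The Data analysis section then names the test: "Non-parametric chi square tests will be performed to explore associations between the socio-demographic variables and the confidence and competence scores". Next, the two kinds of score are to be correlated with each other, and after that: "Based on the results, regression models will be used". The article mentions no adjustment for institution, no ICC and no significance level.

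**The concern.** The Pearson chi-square test takes its null distribution from independent observations. Students at one institution share its teachers, curriculum and facilities, and the quality assurance process acts on exactly these. Their scores are therefore likely to be correlated within a site. If the variable tested also differs between sites, the variance that the test assumes under no association is too small, and associations are declared too often.

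This goes beyond missing detail, because the article names a specific test whose main assumption the sampling does not meet. Two things are at stake. The regression step depends on the preceding results, so a spurious association at the screening stage can shape the models. In addition, one aim is to identify contextual factors. That aim is served mainly by focus groups, but contextual and work-related questionnaire items may be constant or strongly clustered within a site, and there the inflation is largest.

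**Working it through.** **Inputs from the protocol.** 31 institutions and 25 to 50 students admitted per programme per year (Setting); 775–1550 students and 170–230 educators (Quantitative data).

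**Assumed, because the protocol does not give them.** A two-sided 5% level; a score ICC between institutions (ρy) of 0.01 to 0.10; an ICC of the tested variable (ρx) of 1 (fixed per institution, such as public or private), 0.10 (moderately clustered) or 0 (spread evenly within sites).

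**Step 1: the protocol's own figure.** 31 × 25 = 775 and 31 × 50 = 1550. The stated student range is thus exactly 31 clusters of m = 25 or m = 50. For educators, 170/31 = 5.5 and 230/31 = 7.4 per site.

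**Step 2: formula.** For an association between two clustered variables, the design effect is DEFF = 1 + (m − 1) × ρx × ρy. The actual error of a nominal 5% test is 2 × [1 − Φ(1.96/√DEFF)].

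Example: m = 25, ρx = 1, ρy = 0.05 gives DEFF = 1 + 24 × 0.05 = 2.20, 1.96/√2.20 = 1.32 and error 0.186.

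| Group | ρx | ρy = 0.01 | ρy = 0.05 | ρy = 0.10 |
|---|---|---|---|---|
| Students, m = 25 | 1 | 0.078 | 0.186 | 0.288 |
| Students, m = 50 | 1 | 0.108 | 0.291 | 0.420 |
| Educators, m = 5.5 | 1 | 0.055 | 0.077 | 0.103 |
| Educators, m = 7.4 | 1 | 0.057 | 0.088 | 0.126 |
| Students, m = 25 | 0.10 | 0.053 | 0.064 | 0.078 |
| Students, m = 50 | 0.10 | 0.056 | 0.079 | 0.108 |
| Any group | 0 | 0.050 | 0.050 | 0.050 |

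**Step 3: simulation of the 2 × 2 chi-square.** Two separate simulations used 31 clusters and 4000 runs per setting, with a factor fixed per institution. At ICC 0.05 and 0.10 they gave:

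| Students per site | First simulation | Second simulation |
|---|---|---|
| 25 | 0.138 and 0.216 | 0.142 and 0.226 |
| 50 | 0.231 and 0.346 | 0.221 and 0.342 |

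Together this is about 14–23% and 22–35%. A t-test on institution means, run in the first simulation, held 0.050 to 0.057. With ρx = 0 the second simulation's chi-square stayed at 0.047 to 0.056.

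**Step 4: why simulation is lower than formula.** In the second simulation the ICC is set on an underlying continuous score. Cutting such a score at the median reduces the ICC to (2/π) × arcsin(ρ): 0.05 becomes 0.032 and 0.10 becomes 0.064. Putting these into the Step 2 formula gives 0.140 and 0.218 for m = 25, and 0.221 and 0.335 for m = 50, which agrees with both simulations. The simulated figures are therefore the ones quoted for students.

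**Step 5: effective sample size.** For a variable fixed per institution at ρy = 0.05 to 0.10, n/DEFF is 775/2.20 = 352 down to 775/3.40 = 228 students, or 1550/3.45 = 449 down to 1550/5.90 = 263. For educators it is 139 down to 117 of 170, or 174 down to 140 of 230. For a variable spread evenly within sites the full n stands.

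**The case against.** The strongest reply is that the quoted sentence concerns socio-demographic variables, most of which are personal characteristics that vary within a site, and that it names neither public/private status nor district as a predictor. This stands and limits the claim. A reader might infer that every planned test is inflated several-fold, or that the effective sample is always 31. Step 2 shows otherwise: inflation depends on the product ρx × ρy and vanishes when the variable is balanced within sites. For educators the clusters are too small for several-fold inflation at these ICCs.

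Three further inferences are tempting and unsupported:

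- **That the regression models ignore institution.** The article does not say what type they are. A mixed model or GEE fits its wording, and a full protocol or SAP, not shown here, may specify one.
- **That the baseline-to-endline comparison is wrong in the same way.** No chi-square is assigned to it. The article says "The latter two tools will be distributed at each selected institution at two time points", so stable institution effects largely cancel between the two surveys, and the design effect above does not describe that contrast.
- **That standard errors are too small.** A chi-square test reports none; the accurate statement is that its null variance is too small.

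It is also fair that the tests are described as exploratory within an exploratory design, that the ICC and the 5% level are assumptions, and that m = 50 supposes every site at its maximum intake with full participation. These points lower the severity and make the size conditional. They do not make an independence-based test suitable for respondents sampled as whole institutions.

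**Conclusion.** The point holds in limited form. The named chi-square tests take no account of nesting in 31 institutions. At an assumed 5% level and score ICC of 0.05 to 0.10, a variable fixed per institution would be declared associated with student scores in about 14–23% of null cases at 25 per site and 22–35% at 50 per site, roughly three to seven times the nominal rate. For educators the corresponding error is about 6–13% over ICC 0.01 to 0.10. For student variables with a site ICC of 0.10 it is at most about 8% (25 per site) or 11% (50 per site), and for variables balanced within sites it stays at 5%.

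The independence problem follows from the document; the size rests on the assumed ICCs and level. Because the affected step is exploratory screening and is not stated to test the intervention effect, this is a worthwhile correction, not a critical flaw.

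**What to change.** In the Data analysis section:

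- Replace the plain chi-square tests with a cluster-adjusted test: a Rao-Scott chi-square, or GEE or a mixed model with institution as the cluster and a small-sample correction because there are only 31 clusters.
- Analyse variables fixed per institution on institution-level summaries.
- State that the later regression models will also account for institution.
- Report the estimated ICC for each score, with the effective sample size beside n for site-level variables.

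Data collection does not change. The cost is some rewording, slightly more analysis work, and wider intervals for variables clustered by site. Results for variables balanced within sites should hardly change.

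### Chi-square tests on multi-item competency scores discard order and information, and the data-driven step to regression leaves the p-values of retained terms hard to read

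*Protocol article*

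**What the plan says.** The Data analysis section of the protocol article sets out one sequence for the two individual-level tools. First, "the self-assessed confidence and competence scores will be calculated for each core competency". Next, "Principal component analysis will be used for data reduction". Then "Non-parametric chi square tests will be performed to explore associations between the socio-demographic variables and the confidence and competence scores". Confidence–competence correlations are also explored, and the sequence ends with "Based on the results, regression models will be used".

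The Quantitative data section describes the tools. For educators: "The tool consists of 97 items distributed across nine core competencies and includes socio-demographic and work-related questions". The number of response points is not given. For students: "It will include 230 items across the seven core competencies, including a seven-point Likert scale for items". The expected numbers are 170–230 educators and 775–1550 students.

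The only cut-points printed are 60% and 80%, and they belong to the institutional quality assurance tool. Research design calls the study exploratory, while the aims in Background include determining effectiveness and a hypothesis is stated.

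**The concern.** A chi-square test works on a table of categories. A competency score that averages many rating items is ordered and takes many values, so it must be cut before the test is usable. Cutting loses information, and the ordinary chi-square statistic also treats low, middle and high as unordered labels. Real associations between, say, educator background and confidence are then easier to miss than the data require, and the result depends on where the cuts fall.

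The second difficulty is the link to regression. If the chi-square results decide which covariates enter, two things follow. The loss of power carries forward, because a true predictor can be dropped at the screen. And the regression p-values of the terms that survive are computed as if no selection on the same data had taken place.

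What is at stake is the quality of the association findings for the two self-assessment tools. The institutional standards categories, the descriptive means, the correlations and the focus groups are not affected.

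**Working it through.** The article gives no alpha, power, effect size or SD, so there is no figure of its own to reproduce. The student range is a head count: 31 × 25 = 775 and 31 × 50 = 1550. The checks below use the article's sample sizes; every other input is an assumption and is named as such.

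**1. How many-valued are the scores?** Educators: 97 / 9 ≈ 11 items per competency. Students: 230 / 7 ≈ 33 items per competency, each on seven points. Even with few response points per item, 11 items give a score with many levels. Principal component scores would also be continuous.

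**2. Information kept after one cut.** For a normal score cut so that a fraction p lies on one side, the efficiency relative to the uncut comparison of means is φ(c)² / [p(1 − p)], where c is the cut-point on the standard normal scale.
- Median split: 0.3989² / 0.25 = 2/π = 0.637, a loss of about 36%.
- A less central cut keeps less. With p = 0.2, φ(0.842) = 0.280 and 0.280² / 0.16 = 0.49.

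**3. Power at 0.4 SD.** Assumptions: normal scores, two equal groups, two-sided 5%, no clustering. For the uncut score, the expected z is 0.4 × √(n/4).
- n = 170: 0.4 × √42.5 = 2.61; power ≈ Φ(2.61 − 1.96) = 0.74.
- n = 230: 0.4 × √57.5 = 3.03; power ≈ Φ(3.03 − 1.96) = 0.86.

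Simulation gives:

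| n | t-test, uncut score | chi-square, median split |
|---|---|---|
| 170 (educators) | 0.739 | 0.593 |
| 230 (educators) | 0.849 | 0.703 |
| 775 (students) | 0.9997 | 0.994 |
| 1550 (students) | 1.00 | 1.00 |

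The educator chi-square figures are slightly flattering. A second simulation of these rows gave 0.596 and 0.715, and in it the uncorrected test rejected 6.3–6.5% of the time under the null. With continuity correction its power was 0.475 at n = 170 and 0.618 at n = 230.

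**4. Effects for which the uncut test has about 80% power.** Same assumptions, with the effect set separately at each n:

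| n | effect (SD) | t-test | median-split chi-square | tertile chi-square |
|---|---|---|---|---|
| 170 | 0.430 | 0.797 | 0.661 | 0.607 |
| 230 | 0.369 | 0.804 | 0.658 | 0.593 |
| 775 | 0.201 | 0.801 | 0.608 | 0.610 |
| 1550 | 0.142 | 0.808 | 0.626 | 0.608 |

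So the student analysis is safe for a 0.4 SD difference but loses similar power at 0.14–0.20 SD. Three groups do not rescue the test, because it ignores their order.

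**5. If the regression follows a significance screen.** Simulated with no true associations, 5 or 10 independent binary covariates, a median-split chi-square screen, then ordinary least squares on the uncut score with the selected covariates only (n = 200 and 1000):

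| Screen | null covariate significant, given that it was selected | per candidate covariate |
|---|---|---|
| p < 0.05 | 42–44% | 2.1–2.4% |
| p < 0.20 | 20–22% | 3.8–4.1% |

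The columns are linked: rate per candidate = selection rate × rate given selection. For n = 200 with 5 covariates and the 0.05 screen, 0.024 / 0.424 ≈ 0.057 is the selection rate. At least one false positive arose in 10–33% of screened runs and in 22–40% of runs with all covariates entered. Screening therefore distorts how a retained term's p-value should be read; it does not raise the overall number of false positives.

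**6. Cost of the screen for a true effect.** At n = 170 and 0.4 SD, a p < 0.05 chi-square screen would drop the predictor in about 1 − 0.59 = 41% of studies, against 1 − 0.74 = 26% with a test on the uncut score.

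**The case against.** The strongest reply is that the article describes exploration and nothing more. The design is labelled exploratory, no alpha or confirmatory reading is attached to these p-values, and socio-demographic associations are not among the three listed aims. No screening threshold or entry rule is written, and the results on which the regression depends could be the components or the correlations just as well as the chi-square tests. Cut-points, covariate lists and model type may stand in a fuller plan, and the educator tool may have cut-points in sources not shown.

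Much of this stands. The absence of cut-points from a condensed article is not itself a fault, and nothing says that the regression will use categorised scores. But the choice of chi-square for these scores is stated, not omitted, and an analysis on the original scale is just as exploratory.

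Three stronger readings are tempting, and the document does not support them.
- That the regression p-values are invalid outright. This needs a screening rule that is not written, and even with one the error per candidate covariate stays below 5% in the check above.
- That many false positives enter because of the chi-square step. There are (9 + 7) × 2 = 32 scores before any data reduction; with an assumed 8 covariates that is 256 tests and 256 × 0.05 = 12.8 chance findings. Entering all 8 covariates in 32 models produces the same count, so this is no argument for the change.
- That the loss is equally serious in both groups. The seven-point scale is documented only for students, and at their numbers the loss for a 0.4 SD difference is negligible.

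**Conclusion.** The concern holds as a moderate point about an inefficient stated method. Chi-square tests on these scores discard order and, with a median split, about 36% of the information. For educators this costs about 15 percentage points of power at 0.4 SD (74% to 59% at n = 170; 85% to 70% at n = 230). For students the cost appears only for smaller effects. The step to regression is ambiguous. If it is significance screening, p-values of retained terms lose their nominal level (about 20–44% for a selected null covariate instead of 5%); if it is not, that part falls away.

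The figures rest on normal scores, equal groups, independent binary covariates, the chosen screen thresholds and no clustering by institution. The 0.4 SD difference is illustrative and does not come from the article. The direction of the loss does not depend on that choice.

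**What to change.** In Data analysis, replace the chi-square tests on scores with a regression of each competency score, or each principal component score, on its original scale: linear, or ordinal if the distribution requires it, and allowing for institution. Name the socio-demographic covariates in advance, enter them together whatever their significance, and report estimates with 95% confidence intervals. Keep chi-square for pairs of variables that are both genuinely categorical. Replace the sentence that makes regression depend on the results by one that names the outcome and covariates; if any data-driven selection is kept, state that its p-values are descriptive.

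The cost is a change of wording, somewhat more modelling work and commitment to a fixed covariate list. Data collection and software are unchanged. The change improves precision and makes the p-values interpretable, but it does not reduce the number of chance findings expected over many scores and covariates, so results should still be presented as exploratory.
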